### **6.5 Description and justification of route of administration and dosage**

This is the first study to investigate the administration of vitamin K during COVID-19, and there is no dosage that has been previously shown to correct the deficiency. Available data indicates that the total vitamin K deficiency is quite severe, comparable to that seen in hemodialysis patients [26, 53].

Therefore, the current study will use the dosage 1000µg/day, which is comparable to the highest dosage previously studied in healthy persons and hemodialysis patients [46, 47, 50], see also section 6.4.

### **6.6 Dosages, dosage modifications and method of administration**

Vitamin K2 MK-7 will be administered as tablets taken orally, either swallowed by the patient, or pulverized and administered as a suspension in water through a nasogastric tube in case a patient is unable to swallow the product.

The total daily dosage will be 1000µg/day, there will be no dosage modification during the trial.

### **6.7 Preparation and labelling of Investigational Product**

In this study Vitamin K2 MK-7 will be administered orally according to the manufacturer's instructions. Boxes containing either 42 tablets of 333 µg vitamin K2 MK-7 or 42 tablets of placebo will be delivered by Kappa Biosciences AS to the pharmacy of the Canisius Wilhelmina Hospital. These will be labelled with numbers 1 to 40, see section 8.2 on randomization.

After inclusion into the study a patient will be issued a box of study product (either Vitamin K2 MK-7 or placebo). Upon issue the study nurse or investigator will fix a second label with the patient's name and hospital ID number to the box to avoid any chance of accidental study product switching if two patients enrolled in the study are staying in the same room.

If a patient is unable to swallow the product but has a nasogastric tube Vitamin K2 can be administered via this route. A nurse will pulverize the tablets and create a suspension in water that can be passed through the tube.

### **6.8 Drug accountability**

The principal investigator must ensure that Vitamin K2 MK-7 and placebo are stored in a climate controlled environment according to the guidelines of the manufacturer. Accurate records must be maintained regarding the receipt of both Vitamin K2 MK-7 and placebo which include: date received, lot number, amount received.

Accurate records must also be maintained regarding issuing of Vitamin K2 MK-7 and placebo. This includes:

- Patient identification number
- Date and box code number
- Signature of the person issuing the trial medication

After the product has been issued treating nurse will be responsible for verifying the administration of the study product and noting this in the electronic patient system according to local hospital protocols.

## **7. NON-INVESTIGATIONAL PRODUCT**

All subjects will be treated with at least a prophylactic dosage of heparin-based (heparin or any low-molecular weight heparin) anticoagulants according to local hospital protocols.

### **7.1 Name and description of non-investigational product(s)**

Non-investigational medicinal product: heparin or low-molecular weight heparins (including enoxaparin, nadroparin and dalteparin)

### **7.2 Summary of findings from non-clinical studies**

For more information on the structure and function of heparins and low-molecular weight heparins, see Farmacotherapeutisch Kompas.

In short, at therapeutic dosages heparin exerts its anticoagulant effect by inhibiting the function of activated coagulation factors X and II in an antithrombin (AT)-dependent manner [54]. In prophylactic dosages heparin only inhibits the function of activated factor X. Low-molecular weight heparins have a similar mechanism of action, but tend to have stronger inhibitory activity to factor X and weaker inhibitory activity towards factor II. Unlike nadroparin and dalteparin, enoxaparin also has weak activity against factor VII.

The therapeutic and prophylactic effects of all heparin-based anticoagulants are independent of vitamin K status.

### **7.3 Summary of findings from clinical studies**

Low-molecular weight heparins are used extensively for thrombosis prophylaxis and treatment of thromboembolic diseases in patients admitted to the hospital and in out-patient settings. There is a broad body of data indicating their safety is comparable or superior to oral anticoagulant drugs [55, 56].

Recently a high number of thromboembolic complications were seen in COVID-19 patients, especially those admitted to the ICU [2]. Based on these findings national guidelines were revised to encourage use of thrombosis prophylaxis in all COVID-19 patients without significant contra-indications.

### **7.4 Summary of known and potential risks and benefits**

The major risk of heparin or low-molecular weight heparins are bleeding. Current guidelines advise the use of prophylactic dosages of these anticoagulants in COVID-19 patients because the risk of major thromboembolic complications in these patients are thought to outweigh the risks of bleeding complications.

### **7.5 Description and justification of route of administration and dosage**

All subjects will be treated with at least a prophylactic dosage of heparin-based (heparin or any low-molecular weight heparin) anticoagulants according to local hospital protocols.

Patients with an indication for therapeutic dosages of anticoagulants, including patients who upon admission use VKAs or DOACs, must be switched to a therapeutic dosage of heparin or any low-molecular weight heparin according to local hospital protocols and the discretion of the treating physician, prior to inclusion in the study.

### **7.6 Dosages, dosage modifications and method of administration**

If patients develop thromboembolic complications during the study or are admitted to an ICU they can be treated with therapeutic dosages or higher prophylactic dosages of heparin-based anticoagulants, respectively, without being excluded from the study.

If during the course of this study local treatment guidelines on use of prophylactic or therapeutic anticoagulants in COVID-19 patients change, patients will be treated in accordance with those updated guidelines. If investigators believe the updated protocol increases the risks associated with participation in this clinical trial, this will be communicated to the reviewing Medical Ethical Committee as a protocol amendment.

### **7.7 Preparation and labelling of non-investigational product**

This will be done according to local hospital protocols and specific manufacturer's instructions.

### **7.8 Drug accountability**

Drug administration will be recorded by the treating nurse in the electronic patient system according to local hospital protocols.

## 8. METHODS

### 8.1 Study parameters/endpoints

#### 8.1.1 Main study parameters/endpoints

- Plasma desmosine levels before and during vitamin K supplementation in intervention versus control patients
- Plasma dp-uc MGP levels before and during vitamin K supplementation within the intervention group and in intervention versus control patients

#### 8.1.2 Secondary study parameters/endpoints

- Difference between the number of grade 3 and grade 4 adverse events between the intervention and control group, with special attention for: progression of respiratory insufficiency, thrombotic events, pulmonary embolism or deep venous thrombosis, bleeding, renal insufficiency, cardiac decompensation, liver enzyme abnormalities and/or liver failure.
- Changes in serum PIVKA-II levels during COVID-19 with or without vitamin K supplementation

#### 8.1.3 Exploratory study parameters

- Serum (undercarboxylated) protein S levels before and after vitamin K supplementation
- Incidence of respiratory failure defined as either intubation and mechanical ventilation or death (with respiratory failure as a likely direct or indirect cause of death) in the intervention versus control group
- Change in disease severity as measured by low-dose chest CT at baseline and on day 5 in intervention versus control groups
- Plasma levels of active MGP before and after vitamin K supplementation
- Normative APC sensitivity ratio and prothrombin (Echis Carinato test) and TFPI concentration before and after vitamin K supplementation
- Inflammatory parameters including CRP, d-dimer, ferritin, IL-6, TNF- $\alpha$ , IFN- $\gamma$  and s-IL-2r as measured by ELISA or Multiplex in both intervention and control groups
- Other markers related to the pathogenesis, susceptibility and severity of COVID-19 in both intervention and control groups
- Vitamin K epoxide reductase complex subunit 1 (VKORC-1) gene polymorphisms and vitamin D receptor gene polymorphisms

## 8.2 Randomisation, blinding and treatment allocation

Forty patients will be allocated receive either vitamin K2 MK-7 supplementation or placebo in a double-blind manner.

20 boxes containing tablets of Vitamin K2 MK-7 and 20 boxes containing placebo tablets will be manufactured by Kappa Biosciences AS and randomly assigned numbers from 1 to 40 as follows.

Prior to the study start a treatment randomization list will be generated using the Microsoft Excel command ASELECTUSSEN (0,1000). Someone from the Canisius Wilhelmina Hospital pharmacy will be responsible for performing the randomization and for assigning treatment numbers to either the intervention or placebo group. A second pharmacy employee, not involved in the assignment, will check to see if randomization is done correctly. Using Excel, the treatment numbers 1 to 40 will be linked to a randomization number between 0 and 1000. The treatment numbers with the twenty lowest randomization numbers will be assigned the vitamin K2 MK-7 boxes and treatment numbers with the twenty highest randomization numbers will be assigned to the placebo boxes. If two identical numbers are produced, the whole procedure is repeated. The master randomization list is kept at the Canisius Wilhelmina Hospital pharmacy.

Using this procedure the CWZ pharmacy will generate a list of treatment numbers 1 to 40 followed by either 'Vitamin K2 MK-7' or 'placebo' and send this list via a secure e-mail to the representative of Kappa Biosciences AS delegated to perform the assignment of treatment numbers to the product boxes. Kappa Biosciences AS will label the intervention and placebo boxes according to the list generated by the pharmacy.

Once a patient is included into the study they will be assigned to the lowest a treatment number still available at the trial site. Treatment number will be registered on the drug accountability log (section 6.8) and in the eCRF.

This is a double blind study: patients, treating physicians, investigators and those performing laboratory analysis and other outcome assessments will be blinded to the identity of study groups until all patients complete primary endpoint assessments (occurring on the last day of treatment of the last patient).

The randomization list is kept by the CWZ pharmacy. A patient's treatment allocation can be deblinded by the CWZ pharmacy at the request of the treating physician by one of the investigators only after discussion with the principle investigator. The allocation will only be deblinded if it is absolutely necessary for the safety of the patient. If the code is broken it will be documented.

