#### **8.3.3 Follow-up of adverse events**

Adverse events will be monitored until discontinuation of treatment, at 28 days post inclusion mortality will be assessed.

When recording adverse events special attention will be paid to progression of respiratory insufficiency, thrombotic events, pulmonary embolism or deep venous thrombosis and bleeding. Toxicities will be scored according to the most recent version of the NCI Common Terminology Criteria for Adverse Events (CTCAE) version 5 (see Appendix).

The treating physician will determine whether adverse events require additional testing, such as, for example, pulmonary CT angiography in the case of suspected pulmonary embolism or coagulation parameters in the case of bleeding.

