### **8.3.6 Dp-ucMGP**

At baseline (within 24 hours of inclusion) and subsequently three times per week, EDTA plasma will be frozen at -80 degrees Celsius for retrospective determination of dp-ucMGP. Circulating dp-ucMGP levels will be determined using the commercially available IVD CE marked chemiluminescent InaKif MGP assay on the IDS-iSYS system (IDS, Boldon, UK). 50 µL of patient sample or calibrators are incubated with magnetic particles coated with murine monoclonal dpMGP antibody, an acridinium labelled murine monoclonal ucMGP antibody and assay buffer. The magnetic particles are captured using a magnet and a wash step performed to remove any unbound analyte. Trigger reagents are added, the resulting light emitted by the acridinium label is directly proportional to the concentration of dp-ucMGP in the sample. The within-run and total precision of this assay is 0.8 – 6.2% and 3.0 – 8.2%, respectively. The assay measuring range is between 300 – 12,000 pmol/L and was previously found to be linear up to 11,651 pmol/L. Dp-ucMGP values below 500 pmol/L are considered to be in the normal healthy range.

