### **8.3.8 Desmosine**

The rate of elastin degradation will be quantified by measuring plasma (p)DES levels. At baseline (within 24 hours of inclusion) and subsequently three times per week, EDTA plasma

will be frozen at -80 degrees Celsius for retrospective determination of pDES. Subjects with the highest pDES are assumed to have the highest rates of elastin degradation. Isodesmosine and desmosine fractions will be measured separately by liquid chromatography-tandem mass spectrometry as previously described using deuterium-labelled desmosine as internal standard [57, 58].

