### 8.3.12 Study flow chart

|                                                                      | Inclusion      | Hospital admission |                    | Follow-up |
|----------------------------------------------------------------------|----------------|--------------------|--------------------|-----------|
| Study day                                                            | 1              | 2-14   | 15-27  | 28        |
| Eligibility criteria + informed consent                              | X              |                    |                    |           |
| Collection of demographic data and medical history                   | X              |                    |                    |           |
| Physical examination and vital signs                     | X              | X                  | X                  |           |
| Vitamin K2 MK-7 or placebo treatment                                 | X              | X                  |                    |           |
| Collecting (serious) adverse events                                  |                | as necessary       |                    |           |
| Collecting adverse events                                            |                | X                  |                    | X         |
| Laboratory testing                                     | X  | X                  | X                  |           |
| dp-ucMGP, PIVKA-II, desmosine                          | X  | X                  | X                  |           |
| Plasma and serum collection for exploratory endpoints  | X  | X                  | X                  |           |
| CT scan                                                              | X  | X      |                    |           |

 Vital signs are collected at least 3 times per day until discharge, physical examination is performed as necessary

 Blood is collected three times per week while the patient is admitted to the hospital

 Full blood count, electrolytes (sodium, potassium, calcium), creatinine, liver enzymes (bilirubin, ALAT, ASAT and LDH), c-reactive protein (CRP) and albumin; d-dimer will be determined at all follow-up time points (though not at baseline)

 Analysis performed retrospectively

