### **10.1 Primary study parameters**

The primary outcome of difference in dp-ucMGP (log-transformed values) will be assessed by comparing samples pre- and post-treatment using a matched-samples t-test and between groups using an independent samples t-test. Desmosine (log-transformed values) will be compared between the intervention and control groups using an independent samples t-test. Additionally, ANCOVA testing can be performed for both outcome measurements.

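### Section 8.2 lets the blind end on the last patient's last treatment day, so blinding is not guaranteed through the retrospective primary assays or day-28 follow-up

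*Protocol*

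**What the plan says.** Section 8.2 calls the trial double-blind and lists who is covered: patients, treating physicians, investigators and laboratory and outcome staff. Of the last group it says that "those performing laboratory analysis and other outcome assessments will be blinded to the identity of study groups". The blind then holds "until all patients complete primary endpoint assessments (occurring on the last day of treatment of the last patient".

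Other sections describe when measurement takes place:

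- Desmosine (section 8.3.8): EDTA plasma "will be frozen at -80 degrees Celsius for retrospective determination of pDES".
- Dp-ucMGP (section 8.3.6): "EDTA plasma will be frozen at -80 degrees Celsius for retrospective determination of dp-ucMGP".
- Flow chart (section 8.3.12): the row for dp-ucMGP, PIVKA-II and desmosine carries footnote 4, "Analysis performed retrospectively". The same row is marked for days 15-27, and footnote 2 says "Blood is collected three times per week while the patient is admitted to the hospital".
- Follow-up: section 8.3.3 says "at 28 days post inclusion mortality will be assessed", and sections 3 and 9.2.2 place follow-up of serious adverse events on day 28 as well.

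No section extends the blind to the end of the assays, to day 28 or to database lock.

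**The concern.** The parenthesis in section 8.2 turns an event, completion of the primary endpoint assessments, into a date, the last day of treatment. The two do not coincide. On that date the last on-treatment blood sample has at most been drawn; its desmosine and dp-ucMGP values do not yet exist. The people who will produce them are among those whose blind the rule allows to end.

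If the rule is followed literally, decisions on re-running an assay or excluding a value could be taken with the allocation known, for both primary endpoints and for PIVKA-II, a secondary endpoint. The trial could then no longer say that its laboratory and outcome assessment was blinded. Once lifted, the blind cannot be restored.

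Day-28 follow-up is a second and separate exposure. It does not touch the primary endpoints, but causality grading of serious adverse events (section 9.4.2) and attributing a death to respiratory failure (an exploratory endpoint in section 8.1.3) both involve judgement.

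**Working it through.** The plan gives no figure on this point to reproduce. The check sets the stated end of the blind against the stated times of measurement and follow-up.

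**Inputs**

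- End of blind: last treatment day of the last patient (section 8.2).
- Last treatment day: day 14 at the latest, or discharge if earlier (sections 3 and 5.1).
- Expected average stay: 6 days (section 3).
- Follow-up of mortality and serious adverse events: day 28 (sections 3, 8.3.3 and 9.2.2).
- Assay timing: retrospective, on frozen samples, with no date and no batching rule (sections 8.3.6 and 8.3.8; flow chart footnote 4). For PIVKA-II the timing rests on footnote 4, because the storage sentence in section 8.3.7 names dp-ucMGP instead.
- Accrual rate: not given.

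**Step 1. Primary assays.** The gap between permitted unblinding and assay cannot be computed, because no assay date is given. It can be bounded by reasoning:

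- Samples from the last patient's last treatment days are frozen for later determination, so their assay almost certainly falls after the permitted unblinding.
- Samples from earlier patients may be assayed before or after it. If all are run in one batch after the last patient, every primary value is produced after it.

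**Step 2. Late samples.** Treatment ends by day 14, but the flow chart marks marker sampling on days 15-27 while a patient is admitted. For a last patient with a long stay, some marker samples could be drawn, not just assayed, after the permitted unblinding. Section 3 says instead that sampling stops when treatment stops, so this exposure depends on which text is followed.

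**Step 3. Day-28 follow-up of the last patient.** Gap = 28 − last treatment day.

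- Treatment to day 14: 28 − 14 = 14 days.
- Last treatment day 6, taking the average stay as the length of treatment: 28 − 6 = 22 days.

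A discharge before day 6 would lengthen the gap. Section 8.4 words the 28 days as running from treatment rather than inclusion, which would not shorten it.

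**Step 4. Other patients short of day 28.** Assume even accrual at r patients per week, and that the last patient enrolled is the last to stop treatment, on day L. The number with day 28 still ahead is about 1 + floor((28 − L − 1) × r / 7).

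| Assumed r per week | L = 14 | L = 6 |
|---|---|---|
| 1 | 1 + floor(13/7) = 2 | 1 + floor(21/7) = 4 |
| 2 | 1 + floor(26/7) = 4 | 1 + floor(42/7) = 7 |
| 4 | 1 + floor(52/7) = 8 | 1 + floor(84/7) = 13 |

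So 2 to 13 of the 40 patients would be short of day 28 over this assumed range.

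**Step 5. Is the date a lone slip?** Sections 9.4.3 and 12.9 also place the end of the study at discontinuation of treatment in the last patient, despite day-28 follow-up. The same date recurs, so it is unlikely to be corrected in practice without a change to the text.

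**The case against.** The strongest reply is that the operative condition in section 8.2 is completion of the primary endpoint assessments, and that the parenthesis only misdates it. The section expressly blinds the laboratory, which suggests an intent to hold the blind through assay. The word until sets how long the blind must last at least. Nothing orders the list to be released on that day, and it stays at the hospital pharmacy. This stands as to intent, but the text still names a date on which the obligation ends, and no other section overrides it.

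Second, the assays leave limited room for bias. Desmosine is measured by mass spectrometry with a labelled internal standard, and dp-ucMGP by a commercial chemiluminescent assay on an analyser. Shipped samples carry only the trial name and study code (section 12.5). This stands as to size. Coding hides identity rather than allocation, though: the treatment number is in the eCRF, so a released list could be linked to study codes.

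A reader might infer several stronger points that the protocol does not support:

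- *That all primary samples will be assayed unblinded, or that the primary endpoints are simply unprotected.* Retrospective means after the draw, not necessarily after the last patient.
- *That the 14 to 22 days measure the harm to the primary endpoints.* They concern day-28 follow-up only. Vital status is objective, 28-day mortality is not a listed endpoint in section 8.1, and the secondary endpoint of grade 3 and 4 events is recorded only until treatment stops (section 9.2.1).
- *That CT reading will be unblinded.* CT is exploratory, the second scan is due by about day 5, and no text defers the reading. The radiologist's manual adjustment is a reason to include CT in the fix, not evidence of a problem.
- *That the analysis model will be chosen after unblinding.* Section 10.1 does say "Additionally, ANCOVA testing can be performed for both outcome measurements", but a statistical analysis plan that is not shown may settle that choice.

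**Conclusion.** The point holds as an internal contradiction. The protocol promises blinded laboratory and outcome assessment, then lets the blind end on a date by which its own schedule shows the primary measurements need not be finished. This is a stated rule that is wrong as written, not a detail left for a later document.

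Blinding through assay is not guaranteed for either primary endpoint or for PIVKA-II. The exposure is near-certain for the last samples and complete only if the assays are batched at the end. For the last patient, day-28 follow-up comes 14 to about 22 days after the permitted unblinding; the lower figure follows from the day-14 limit on treatment, and the upper one assumes treatment for the expected 6-day stay. The count of other patients affected rests wholly on assumed accrual.

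The likely bias in the primary biomarkers is modest. The case for acting is that the correction costs little and the blind cannot be recovered once lifted.

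**What to change.** In section 8.2, remove the parenthesis and replace the end point of the blind with wording such as:

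> *The blind is kept for all roles named above until all desmosine, dp-ucMGP and PIVKA-II assays and all CT readings are complete and the day-28 follow-up of the last patient has been recorded. The closed session of the Safety Monitoring Committee and documented emergency unblinding are exempt.*

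Both exemptions already exist in the protocol (sections 9.5.1 and 10.3 for the committee, section 8.2 for emergencies), so the change leaves safety oversight as it is.

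The cost is one sentence and a delay of some weeks in unblinding: at least the 14 to about 22 days to the last day-28 check, and longer if the assays finish later.
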